## Abstract

**Background:**

The optimal post-operative care regimen after surgically fixed Lauge Hansen supination exorotation injuries remains to be established. This study compares whether unprotected weight bearing as tolerated is superior to protected weight bearing and unprotected non-weight bearing in terms of functional outcome and safety.

**Methods/Design:**

The WOW! Study is a prospective multicenter clinical trial. Patients between 18 and 65 years of age with a Lauge Hansen supination exorotation type 2, 3 or 4 ankle fractures requiring surgical treatment are eligible for inclusion. An expert panel validates the classification and inclusion eligibility. After surgery, patients are randomized to either the 1) unprotected non-weight-bearing, 2) protected weight-bearing, or 3) unprotected weight-bearing group.

The primary outcome measure is ankle-specific disability measured by the Olerud-Molander ankle score. Secondary outcomes are 1) quality of life (e.g., return to work and resumption of sport), 2) complications, 3) range of motion, 4) calf wasting, and 5) maximum pressure load after 3 months and 1 year.

**Discussion:**

This trial is designed to compare the effectiveness and safety of unprotected weight bearing with two commonly used post-operative treatment regimens after internal fixation of specified, intrinsically stable but displaced ankle fractures. An expert panel has been established to evaluate every potential subject, which ensures that every patient is strictly screened according to the inclusion and exclusion criteria and that there is a clear indication for surgical fixation.

**Trial registration:**

The WOW! Study is registered in the Dutch Trial Register (NTR3727). Date of registration: 28-11-2012.

## Background and rationale

Ankle fractures in adults occur frequently with an annual incidence of approximately 100 to 180 fractures per 100,000 people each year [1-3]. Most ankle fractures occur after inversion or eversion twisting trauma and sports injuries. For stable non-displaced ankle fractures, a conservative treatment with a splint or cast is indicated [4,5]. However, when the congruity of the ankle fork or the joint stability is compromised, open reduction and internal fixation is required to attain full function of the ankle joint [6,7].

While indications for surgical treatment are rather well defined, controversy exists with regard to the optimal postoperative care regimen [8]. Post-operative care regimens vary widely from plaster casts and functional bracing to unprotected non-weight bearing and weight bearing [9-15]. Prior studies show a possible advantage of (protected) weight bearing over (protected) non-weight bearing and of functional mobilization over non-functional mobilization with crutches [11,16]. Some recent, small retrospective and matched control studies even suggested that early (unprotected) weight bearing results in faster recovery and better ankle function [11-13].

The objective of this trial is to compare functional outcome and safety after three different post-operative care regimens: 1) unprotected non weight bearing, 2) protected weight bearing, and 3) unprotected weight bearing.

## Methods and design

### Study design

This is a prospective multicenter randomized controlled trial involving six hospitals in the Netherlands. The study has been approved by the local Institutional Review Board under protocol number WOW-01/NL40835.100.12. This study compares three different post-operative care regimens after ankle surgery; all patients with a Lauge Hansen supination exorotation type 2, 3 or 4 ankle fractures requiring surgical treatment are eligible for inclusion.

After registration of the patient, an anonymous X-ray is sent to an expert panel consisting of six experienced orthopedic trauma surgeons. The fracture is classified according to the Lauge Hansen classification and advice on whether or not operative fixation is indicated is provided within 24 hours. A patient is eligible for inclusion when a majority of the expert panel agrees that operative fixation is necessary and the fracture type meets the inclusion criteria. When votes are split equally, the chairman (LL) is the tiebreaker. A flow chart of the study is shown in Figure 1.

**Figure 1 Fig1:**
[figure not shown]
Flowchart WOW! Study.

### Patient population

Non-pregnant, Dutch speaking patients are being recruited from the participating hospitals in the emergency room or pre-operatively during an outpatient department visit. Patients are screened for eligibility according to the inclusion and exclusion criteria (Table 1). The treating physician or study staff explains the study and informed consent is obtained from each patient. Retrospective data of the participating hospitals shows that approximately 395 patients per year undergo surgery for ankle fractures. Approximately 20% of these patients would be eligible for enrollment according to our inclusion criteria. If this trend continues, we anticipate enrollment of 79 patients per year (Table 1).

**Table 1 Tab1:** **Inclusion and exclusion criteria**

**Inclusion criteria**	**Exclusion criteria**
Age ranging from 18–65 years	Pre-existent impaired mobility
Fractures classified as Lauge Hansen supination eversion type 2–3 or 4	Expected insufficient stable fracture fixation with standard surgical technique
Articular discongruity of >2 mm on X-ray	Pre-existent cognitive disability
	Necessity for a syndesmosis screw
	Tertius fragment requiring operative fixation
	Body mass index >30
	Diabetes mellitus
	Polytrauma patients (ISS ^a^ >16 or >2 AIS ^b^ regions involved)
	Gustillo 2 and 3 open fractures
	Inability to comply with non-weight-bearing mobilization
	Inability to comply with follow-up

^a^Injury Severity Score.

^b^Abbreviated Injury Scale.

### Inclusion and exclusion criteria

All patients between 18 and 65 years with a Lauge Hansen supination exorotation type 2, 3 and 4 ankle fractures are eligible for inclusion (Figure 2). Exclusion criteria include pre-existent impaired morbidity, cognitive disability, body mass index >30, and diabetes mellitus. All inclusion and exclusion criteria are listed in Table 1.

**Figure 2 Fig2:**
[figure not shown]
Lauge Hansen classification. Trauma mechanism of ankle fractures. Supination abduction: 1. Talofibular ligament sprain or fibular avulsion; 2. Vertical medial malleolus fracture. Supination eversion: 1. anterior tibiofibular ligament sprain; 2. Lateral oblique fibular fracture; 3. Avulsion of posterior malleolus or ligament rupture; 4. Transverse medial malleolus fracture or disruption of deltoid ligament. Pronation abduction: 1. Transverse medial malleolus fracture or deltoid ligament; 2. Anterior tibiofibular ligament sprain; 3. Transverse comminuted fracture of the fibula. Pronation exorotation: 1. Transverse medial malleolus fracture or deltoid ligament disruption; 2. Anterior tibiofibular ligament disruption; 3. Oblique or spiral fracture of the fibula; 4. Avulsion of posterior malleolus of posterior tibiofibular ligament.

### Randomization process

Patients are randomized using computerized block randomization to either protected weight bearing, unprotected non-weight bearing, or unprotected weight bearing. The randomization is stratified by the participating hospitals. The blocks for randomization consist of 21 patients with the three post-operative care regimens equally represented in each block. Follow-up is by the intention-to-treat principle. Following surgical fixation, the treating surgeon logs into the private website where the patient is randomized to one of three post-operative care regimens.

### Postoperative management and follow-up

Patients are treated during same day admission if possible. According to their post-operative care regimen, patients receive a cast, exercise instructions, and a physiotherapist referral letter. All patients are reviewed in the outpatient clinic by the treating surgeon and/or investigator at 2 weeks, 6 weeks, 3 months, 6 months, and 1 year after surgery. At all post-operative outpatient visits, a standardized clinical exam is conducted including three standardized patient reported outcome questionnaires; the Olerud Molander Ankle Score (OMAS), the Short Form-36 (SF-36), and the Visual Analogue Scale (Table 2).

**Table 2 Tab2:** **Study assessments by time-point**

**Time point**	**Intake**	**2 weeks**	**6 weeks**	**12 weeks**	**6 months**	**1 year**
OMAS^a^	**X**		**X**	**X**	**X**	**X**
SF-36^b^	**X**			**X**		**X**
Wound inspection		**X**	**X**			
Calf circumference			**X**	**X**	**X**	**X**
Range of motion			**X**	**X**	**X**	**X**
Demographics	**X**					

^a^Olerud Molander Ankle Score.

^b^Short Form 36.

### Primary outcome measures

The OMAS is a scoring scale for symptom evaluation in patients with an ankle fracture and in patients with other acute ankle injuries [17]. This score ranges from 0 to 100%, with 100% representing normal ankle function [17]. It was developed specifically as a comparative research measure to improve consistency and uniformity in ankle injury reporting [17]. A difference of 5 to 10 points between two groups on the OMAS is defined as a clinically relevant result.

### Secondary outcome measures

The SF-36 is one of the most widely used generic health questionnaires. It was developed as a medical outcome score to measure the functional health status of a patient [18,19]. It has been translated into Dutch and validated as a useful questionnaire to assess a broad array of health-related quality-of-life issues [19].

Other secondary measures of function include range of motion (ROM) (plantar and dorso-flexion), weight-bearing pressure load, and calf wasting (difference in calf circumference at enrollment and at 12 weeks post-operative) of the injured ankle. Pain is measured by the Visual Analogue Scale on an 11-point Likert scale. Return to work and sports is also recorded. The pressure load of the injured and non-injured ankle is measured by a scale at every visit, starting at 6 weeks.

Post-operative complications are defined as 1) wound healing problems (no interventions required), 2) superficial wound infections (requiring oral antibiotic treatment based on a wound culture), 3) infection near hardware (requiring surgical debridement and intravenous antibiotic treatment based on a deep tissue culture), 4) hardware failure (requiring re-operation), 5) mal-union or non-union (clinically and radiographically confirmed), and 6) deep venous thrombosis (confirmed by ultrasound).

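### Calf wasting is defined as change from enrolment, but Table 2 schedules no calf measurement at intake; the text and Table 2 also disagree on OMAS, SF-36 and VAS visits

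*Protocol article*

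**What the plan says.** **Calf wasting.** The Abstract lists it as a secondary outcome. Secondary outcome measures defines it as "calf wasting (difference in calf circumference at enrollment and at 12 weeks post-operative". Table 2 has a row for calf circumference with marks at 6 weeks, 12 weeks, 6 months and 1 year. The cells for Intake and 2 weeks are empty.

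**Questionnaires.** Postoperative management and follow-up sets the visits "at 2 weeks, 6 weeks, 3 months, 6 months, and 1 year after surgery". It continues: "At all post-operative outpatient visits, a standardized clinical exam is conducted including three standardized patient reported outcome questionnaires". It names these as the OMAS, "the Short Form-36 (SF-36), and the Visual Analogue Scale (Table 2"). Table 2 marks OMAS at Intake, 6 weeks, 12 weeks, 6 months and 1 year, and SF-36 at Intake, 12 weeks and 1 year. It has no row for the VAS.

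**Pressure load.** Secondary outcome measures says that it "is measured by a scale at every visit, starting at 6 weeks". Table 2 has no row for it. The Abstract's list of secondary outcomes ends with "maximum pressure load after 3 months and 1 year".

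**The concern.** A change from enrolment needs a value at enrolment. Intake is the only pre-operative column in Table 2, and the calf row is blank there. If measurement follows the table, the first term of a named secondary outcome is never collected. A baseline that was not taken before surgery cannot be recovered later, so each further patient enrolled on that schedule loses it for good. Trial status reports 73 of 225 patients already enrolled.

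The questionnaire conflict is less damaging but of the same kind. The visit rule in the text cites Table 2 as its support, and the table does not support it. Which repeated measurements exist for OMAS, SF-36 and pain therefore depends on which part of the article is followed.

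**Working it through.** There is no figure of the plan to reproduce. The check sets the text against Table 2, visit by visit. The text's 3-month visit is taken to be the table's 12-week column.

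| Measure | Time points in the text | Time points in Table 2 | In the text, not in the table |
|---|---|---|---|
| Calf circumference, as the definition needs it | Enrolment, 12 weeks | 6 weeks, 12 weeks, 6 months, 1 year | Enrolment |
| OMAS, post-operative | 5: 2 weeks, 6 weeks, 3 months, 6 months, 1 year | 4: 6 weeks, 12 weeks, 6 months, 1 year | 1: 2 weeks |
| SF-36, post-operative | 5: the same visits | 2: 12 weeks, 1 year | 3: 2 weeks, 6 weeks, 6 months |
| VAS | 5: the same visits | No row | All 5 |
| Pressure load | 4: 6 weeks, 3 months, 6 months, 1 year | No row | All 4 (an omission, see the objection) |

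**Calf wasting.** The outcome is the circumference at enrolment compared with that at 12 weeks. Table 2 supplies the second value and not the first.

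The earliest scheduled value, at 6 weeks, cannot stand in for the baseline. Patients are randomized after surgery, so the 6-week value is taken after randomization. It also falls after six weeks on the assigned regimen, which for the protected group means six weeks in a cast. A change from 6 to 12 weeks would omit the period in which the regimens differ by design.

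**Is the blank cell an extraction fault?** Probably not. The table has six time columns, the rows are consistent with one another, and the Intake column carries marks for three other rows.

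**OMAS and SF-36.** These are direct conflicts. Each has a row in the table, and the marks differ from the text by 5 − 4 = 1 visit for OMAS and 5 − 2 = 3 visits for SF-36. The intake marks for both are not in dispute, because the text's rule concerns post-operative visits only.

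**VAS.** The table has no row, but the sentence that schedules the VAS refers the reader to Table 2. The cited support is absent.

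**Primary outcome.** Sample size and power uses OMAS at 12 weeks. That time point is in the text's visit list and in Table 2, so the two agree where the trial is powered.

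**The case against.** The strongest reply is that this is a condensed article. Hospitals would work from the full protocol and case report forms, which are not shown, and an abbreviated table is normal. Several parts of this stand.

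- **Table 2 is not exhaustive.** It also has no rows for deep venous thrombosis, hardware failure, or mal-union and non-union, all of which the text defines as complications. A missing row is therefore not in itself a contradiction. A reader might count pressure load and return to work and sport as further conflicts, but the documents do not support that. Pressure-load timing is given in the text, and no visit is fixed anywhere for return to work and sport.
- **The Abstract is not a clear third schedule for pressure load.** Its closing phrase may apply to the whole list of secondary outcomes, or may name the times to be reported. Measuring at four visits and reporting two is compatible with the text.
- **Loss of the outcome is not shown to have happened.** A reader might infer that calf wasting is uncomputable for all 225 patients, including the 73 enrolled. That holds only if Table 2 was what hospitals followed. Nothing in the article shows that the intake measurement was or was not taken.
- **Bias between arms does not follow.** If hospitals differed in which visits they collected, data would be lost unevenly across hospitals. Randomization is stratified by hospital with the regimens equally represented in each block, so that loss would fall about equally on the arms. It costs precision and does not by itself bias the comparison.
- **A between-arm comparison of calf size survives.** The 12-week circumference is scheduled, so the arms can be compared on it without a baseline.

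Condensation does not remove the rest. The article gives an explicit definition, an explicit visit rule and an explicit table, and these cannot all be right. A fuller document could show which is intended, but it would not make this text consistent.

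**Conclusion.** The point holds as an internal inconsistency affecting secondary outcomes. Under Table 2, calf wasting as defined has no baseline and cannot be computed. Between text and table, OMAS differs by one post-operative visit (5 against 4), SF-36 by three (5 against 2), and the VAS is at five visits in the text with no row in the table that the text cites. The 12-week OMAS comparison, for which the trial is sized, is unaffected.

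This should be corrected, but it does not threaten the main conclusion. It rests on reading the table extract as intact and on treating 3 months and 12 weeks as one visit. How many patients actually lack a baseline calf value cannot be determined from the article.

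**What to change.** 1. Add calf circumference at Intake to Table 2 for all further patients. From the enrolment reported in Trial status, that is 225 − 73 = 152 patients.
2. Report how many of the patients already enrolled have no intake value. For them, compare the arms on 12-week circumference as a supportive analysis. Randomization keeps that comparison fair. It is less precise where baseline calf size would explain much of the variation between patients.
3. Reconcile Postoperative management and follow-up with Table 2 so that OMAS, SF-36 and VAS each have one schedule, and give the VAS a row.
4. Add a pressure-load row matching Secondary outcome measures, for completeness.

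Redefining calf wasting as injured minus uninjured leg is not recommended as the lead remedy. It replaces a defined outcome during the trial. It also does not help patients already past 12 weeks unless the other calf was measured, and the article mentions the non-injured side only for pressure load.

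The cost is one extra tape measurement per patient at intake and an edit to one table and one paragraph.

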### Sample size and power

Our hypothesis is that ankle-specific disability assessed with the OMAS is less for unprotected weight bearing when compared to protected weight bearing and unprotected non-weight bearing. An *a priori* power analysis for superiority of treatment with unprotected weight bearing has been conducted for this hypothesis. To detect a clinically significant 7-point difference on the OMAS at 12 weeks follow-up between unprotected non-weight bearing and unprotected weight bearing with a standard deviation of 10, α = 0.05, β = 0.90, two-sided test (based on superiority of unprotected weight bearing), and a maximum loss to follow-up of 20%, a sample size of 75 patients per group is necessary. Therefore, a total of 225 patients are needed for this study.

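### The sample size of 75 per group (225) does not follow from its stated inputs, which give 55 per group (165). The gap is on the safe side, but its source is not stated, and β = 0.90 should read power (1−β) = 0.90.

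*Protocol article*

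**What the plan says.** The section Sample size and power of the protocol article prints a complete set of inputs.

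- Difference and contrast: "To detect a clinically significant 7-point difference on the OMAS at 12 weeks follow-up between unprotected non-weight bearing and unprotected weight bearing".
- Variability: "with a standard deviation of 10".
- Error rates: α = 0.05 and β = 0.90.
- Sidedness: "two-sided test (based on superiority of unprotected weight bearing").
- Loss allowance and result: "a maximum loss to follow-up of 20%, a sample size of 75 patients per group is necessary".
- Total: "Therefore, a total of 225 patients are needed for this study".

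Allocation is equal, since the section Randomization process has "the three post-operative care regimens equally represented in each block".

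The hypothesis in the sample size section sets unprotected weight bearing against both other regimens, but the calculation names only one of those contrasts. The section mentions no multiplicity adjustment, rank-test correction or allowance for the interim analysis.

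**The concern.** Where every input is printed, a reader should be able to recover the result. Here the inputs lead to a number well below the one stated, so difference, SD, power and sample size cannot all be as written. Either an input that drove the calculation is missing from the text, or the result is wrong.

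What is at stake is the design basis that the final report will cite. The section Primary outcome measures treats 5 to 10 points as clinically relevant. Whether the trial was built around 6 or 7 points therefore affects how a borderline or null result is read. The size also sets the length of recruitment: at the article's expected 79 patients per year, 60 patients take 60/79 = 0.76 years, about nine months.

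Separately, β is the type II error rate, so β = 0.90 taken literally means 10% power.

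**Working it through.** **Inputs** (Sample size and power): difference 7, SD 10, so standardised difference 7/10 = 0.70; two-sided α 0.05; power read as 0.90; loss 20%; equal groups.

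**Step 1. Reproducing the stated figure.**

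- Normal approximation: n = 2(z₀.₉₇₅ + z₀.₉₀)² / 0.70² = 2(1.960 + 1.2816)² / 0.49 = 42.9, so 43 evaluable per group.
- Two-sample t-test (noncentral t): 43.87, so 44 evaluable per group.
- With 20% loss: 43/0.8 = 53.75, so 54; 44/0.8 = 55.
- Three groups: 3 × 54 = 162 or 3 × 55 = 165.

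The stated 75 and 225 are not reproduced. The gap is 225 − 165 = 60 patients, or 60/225 = 27% of the plan. Inflating by multiplication instead (44 × 1.2 = 52.8, so 53) moves further from 75.

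**Step 2. Whether another common reading gives 75.** Each row changes one thing from Step 1 and divides by 0.8. Where two values appear, they are the normal and t-based results.

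| Reading | Enrolled per group |
|---|---|
| One-sided test | 44–45 |
| Power 0.80 | 42–43 |
| Power 0.95 | 68–69 |
| β = 0.90 taken literally (10% power) | 3–4 |
| Bonferroni, two comparisons (α 0.025) | 64–65 |
| Bonferroni, three comparisons (α 0.0167) | 70–72 |
| α 0.01 | 77–79 |
| Three-group ANOVA, means 0/0/7 | 50 |
| Three-group ANOVA, means 0/3.5/7 | 67 |
| Mann-Whitney, efficiency 0.955 | 59 |
| Mann-Whitney, efficiency 0.864 | 64 |

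None gives 75.

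**Step 3. Which inputs do give 75.** All of these need something that the article does not state.

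- A 6-point difference with SD 10: t-based 59.4, so 60; 60/0.8 = 75.
- A 7-point difference with SD of about 11.7: 60; 60/0.8 = 75.
- Bonferroni for three comparisons combined with a Mann-Whitney correction: 57/0.955 = 59.7, so 60; 60/0.8 = 75.

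**Step 4. What 75 per group delivers.** 75 × 0.8 = 60 evaluable per group. Power by the t-test with SD 10:

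| Difference | α (two-sided) | Power |
|---|---|---|
| 7 | 0.05 | 96.7% |
| 7 | 0.025 | 94.0% |
| 7 | 0.0167 | 91.8% |
| 6 | 0.05 | 90.3% |
| 5 | 0.05 | 77.5% |

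The difference detectable with 90% power at 0.05 is 5.97 points.

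**Step 5. What 55 per group would deliver.** With 44 evaluable per group, power for 7 points is 90% at α 0.05 but 84% at α 0.025. The article gives no source for the SD. If it were 12 (an assumption, for sensitivity only), power for 7 points at α 0.05 would be 77% with 44 evaluable and 89% with 60.

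**The case against.** The strongest reply is that the error does no harm to power. With 60 evaluable per group, power for 7 points stays above 90% at two-sided 0.05 and after a Bonferroni split over two or three comparisons. That stands in full, and it limits the point to how the calculation is reported.

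A second reply is that the larger size may be deliberate. The hypothesis has two comparators, the analysis section plans an ANOVA over three regimens, and an interim analysis at half enrolment may lead to early stopping. Each is a plausible reason to go above 55, and a condensed article may omit the step. This also stands, to the extent that the 60 additional patients cannot be called surplus as a plain fact. It does not remove the point, because the article presents 75 as the result of the inputs it lists, and it is not.

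Three stronger readings are tempting, and the document supports none of them.

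- A reader might infer that the final report could not say what the trial was powered for. It could: outcome, time point, contrast, difference, SD and α are all given, and at least 90% power for 7 points holds if the SD is 10. Only the derivation of 75 cannot be stated.
- A reader might infer that the trial should shrink to 165. Step 5 of the working shows what that would cost for a two-comparator hypothesis or a larger SD.
- A reader might take β = 0.90 as a real planning target of 10% power. It is an evident slip of notation, since 10% power would need only 3 to 4 patients per group.

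**Conclusion.** The point holds as a reporting error. As printed, the inputs yield 44 evaluable and 55 enrolled per group (54 by the normal approximation), 165 in total, against 75 and 225 stated. This takes the power target to be 90%, the test to be a two-sample t-test on the named contrast, and loss to be handled by dividing by 0.8.

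The discrepancy is conservative, and the intended 90% power for 7 points is met if the SD is 10 and loss does not exceed 20%. The additional 60 patients are unexplained unless an unstated input set the size, and the document does not show which input, if any, that was. Severity: a correction to the text, not a must-fix on power grounds.

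**What to change.** Keep the target of 225 and revise the paragraph in Sample size and power.

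1. State the input that actually led to 75 per group, whether a different difference, a different SD, a multiplicity or rank-test adjustment, or something else.
2. Replace β = 0.90 with power (1−β) = 0.90.
3. State what the design delivers. Suggested wording: *With 75 patients enrolled per group and at most 20% loss, 60 evaluable patients per group give about 97% power to detect a 7-point difference and 90% power to detect a 6-point difference in OMAS at 12 weeks (SD 10, two-sided α 0.05).*
4. Only if α is in fact to be split over the two comparisons with unprotected weight bearing, add: *At two-sided α 0.025 for each comparison, power for 7 points is 94%.* The article states no such split, so this sentence must not go in by default.

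The cost is one paragraph, with no additional patients and no change to recruitment.
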